## Abstract

Supplemental Digital Content is available in the text

## Introduction

1

### Background and rationale

1.1

Achieving local anesthesia in children is one of the critical aspects of pain management. A current non-pharmacological mean for attaining painless conservative treatment is presented by the laser analgesia (LA) method.

LA is a non-invasive, non-thermogenic bio-modulation of the dental pulp reactivity aiming for reduction of impulse formation of the pulpal nociceptors. It is hypothesized that laser pulses alter the cell membrane behavior of the pulpal nerve fibers by hyperpolarization and loss of impulse conduction, and thus an analgesic effect is achieved.^[1–3]^

The assessment of changes in pulp's sensory responses can be explored by pulp sensibility testing,^[4]^ such as one delivered through thermal or electric test. The aforementioned tests could be valuable means for investigating the occurrence of any pulpal analgesic effect obtained by dental lasers.

The A-delta nociceptive nerve fibers in the pulp are able to generate a fast, sharp pain that is easily localized^[5,6]^ such as one from rapid temperature change,^[7]^ achieved by application of Cold-test. Еlectric pulp testing (EPT) depends on ionic movement and triggers the A-delta fibers as well, due to their conduction speed and their myelin sheath.

The rationale based on the neurophysiology of the pulp, led to choosing both electric and cold testing as means for evaluating the pulpal analgesic effect of the erbium-doped yttrium aluminium garnet (Er:YAG) pulp laser. To our best knowledge, no study before has implemented the use of Cold-test to complement EPT-results in assessment of LA efficacy.

The pulp sensibility testing, along with the assessment of subjective and objective pain sensation during treatment should help estimate the clinical adequacy of the LA method by finding out if pain-free operative treatment can subsequently be performed.

### Objectives

1.2

The intention of the technique of “pre-emptive LA” is to reduce sensation in that small percentage of patients who may experience unpleasant sensations during caries removal. We hypothesized that when operating at low level densities, the laser energy leads to loss of nociceptive impulse formation by coinciding with the natural resonance frequency (15–20 Hz)^[8]^ of cell membranes of nerve fibers in the dental pulp, leading to an analgesic effect.

The aim of this study is efficacy approbation of a modified protocol for LA with Er:YAG for achieving pulpal analgesia in pediatric patients and quantification of the duration and extent of any effects assessed.

The main objectives are to compare pain felt during treatment in laser and placebo analgesia (PA) control group and to register the reactivity of the pulp towards cold and electrical stimuli before and after inducing laser or PA. The second objectives are to evaluate latency of any analgesic effect, patient experience during analgesic or placebo procedure, as well as heart rate dynamics and need for additional anesthesia during treatment.

### Trial design

1.3

The trial to be conducted is a double-blind controlled clinical crossover experimental study with 2-way repeated measures design. Figure 1 summarizes the enrollment, intervention, and assessment schedule, all of which are in accordance with the Standard Protocol Items for Randomized Trials (SPIRIT) recommendations,^[9]^ shown in Table 1 . Patients and outcomes assessor are blinded for the study. Experimental group in this study consists of permanent upper jaw first molars, receiving pre-emptive LA prior to laser caries ablation, whereas control group consists of contralateral permanent upper jaw first molars with similar defects of the same patient, receiving placebo-analgesia prior to laser treatment.

**Figure 1 F1:**
[figure not shown]
Schedule of enrollment, interventions, and assessments of treatments.

**Table 1 T1:**
[figure not shown]
SPIRIT 2013 checklist: recommended items to address in a clinical trial protocol and related documents^∗^.

**Table 1 (Continued) T2:**
[figure not shown]
SPIRIT 2013 checklist: recommended items to address in a clinical trial protocol and related documents^∗^.

The required number of patients is calculated on the basis of a micro-sample at an accepted level of significance (*P* < .05) and a maximum permissible error *α* < 0.05 and *β* < 0.2. Intention-to-treat concept is chosen as statistical approach for data analysis.

## Methods and analyses

2

### Study setting

2.1

The setting of this trial is the Department of Pediatric Dentistry at the Faculty of Dental Medicine, Medical University of Plovdiv, Bulgaria.

### Eligibility

2.2

#### Inclusion criteria

2.2.1

1.Participants in the study are children 10 to 12 years old, compliant with the cognitive development of the child and the requirement for full root development for diagnostics with electrical pulp testing.2.Children, identified as positive or definitely positive through Frankl behavioral rating scale.3.Children who are not considered medically compromised or medically complex patients. The absence of disease is confirmed by anamnestic interview with a parent or a care-giver of the child and excludes general acute or chronic disease, cognitive impairment.4.Patients, requiring conservative treatment of occlusal or foramen caecum caries on 2 first permanent upper jaw molars without prior restorations or dental sealants. Lesions are to be classified as moderate caries by the International caries detection and assessment system (ICDAS) with code 03 or 04, which do not present spontaneous unprovoked pain, percussion or palpation pain or other symptoms, indicating of pulpal or periodontal pathology. Included are carious lesions only on vital teeth, involving up to half of the dentine thickness.5.Obtained informed consent from parents or gave-givers to participate in the study, in which procedures are explained in appropriate manner (see supplementary data file S1—“Informed consent” and supplementary data file S2—“Information leaflet”).

#### Exclusion criteria

2.2.2

1.Patients who are undergoing therapy with neurological, sedative, analgesic, and/or anti-inflammatory drugs 7 days prior to treatment.2.Children, who are first time ever dental patients.3.Patients who are undergoing treatment or have been treated 6 months prior to inclusion with remineralizing agents.4.Excluded are first molars which are affected by hypoplasia or hypomineralization.

#### Interventions

2.2.3

Dental Er:YAG laser (LiteTouch, Light Instruments LTD) will be used as means to attain analgesia and caries removal. Chosen protocol parameters are modified based on previously conducted studies.^[8,10,11]^

Laser analgesic protocol: Water mist spray set to “maximum,” non-contact handpiece with sapphire tip. Tip-to-tissue distance 10 mm from the tooth neck, achieved by using a spacer. Energy is delivered to the enamel above the gingival margin adjacent to the cemento-enamel junction (perpendicularly towards the dental pulp) on each of the 4 line angles of the tooth for 30 seconds, moving the laser handpiece in a sweeping action. Pulse energy—0.2 W/10 Hz/20 mJ. Follows increase of energy and repetition of protocol—0.6 W/15 Hz/40 mJ. Total duration of LA-induction—240 seconds.

Placebo analgesic protocol: No pulse energy applied. Moving the laser handpiece in a sweeping motion repeating actions to imitate LA placement.

Application parameters during caries ablation: Hard tissue preconditioning: 1.5 W/15 Hz/100 mJ for 1 minute; Enamel removal—3 W/15 Hz/200 mJ; Dentin removal—2 W/10 Hz/200 mJ. Smear layer removal: 2 W/10 Hz/200 mJ. Loss of tooth structure was restored with esthetic composite.

#### Clinical protocol:

2.2.4

First visit:

1.Parents or care-givers are informed about laser technique and get acquainted with the nature of the research being conducted in to prepare their children for the dental treatment. The parent or care-giver signs informed consent.2.Patients are asked to complete Children's Fear Survey Schedule–Dental Subscale (CFSS-DS) questionnaire.3.Pulse-oximeter is connected to patient's index finger. Start of heart rate monitoring and recording—7 minutes prior treatment. Time frame: until end of treatment.4.Blind for chosen method investigator evaluates the initial reactivity of the pulp with EPT 5 minutes prior laser or PA. Four minutes before applying chosen method same investigator performs Cold-test with propane-butane gas, applied on a cotton pad on the tooth. Patient is asked to evaluate pain perception on VAS.5.The chosen method, placebo or LA, is applied.6.Patient experience during LA/PA is evaluated by a patient questionnaire immediately after the procedure. Patient is asked to answer 4 questions with possible answers “yes” and “no”: “Did you feel pain when we put your tooth to sleep?”; “Were you frightened when we put your tooth to sleep?”; “Do you feel any pain now that your tooth is put to sleep?”; “Do you feel any tingling sensation now that your tooth is put to sleep?”.7.Laser ablation of the carious lesion begins. No rotary instruments or other excavation techniques are to be applied.8.Five minutes after the analgesic procedure same investigator evaluates the sensibility of the pulp with EPT and 6 minutes after performs Cold-test on same tooth. Patient is asked to evaluate pain perception after Cold-test on the VAS pain scale.9.At the 20th minute after LA/PA, EPT testing is performed. At the 21st minute a Cold-test is applied and the pain perception is registered on the VAS.10.Outcomes assessor monitors the patient during treatment and registers pain related behavior using Faces, Legs, Activity, Cry, Consolability (FLACC) Behavioral Pain Rating Scale.^[12]^11.Patients who complete the procedure without the need for additional anesthesia, immediately after placement of restoration are asked to use the combined VAS scale to quantify the level of pain felt during treatment. Patients who request that the procedure is terminated to administer an anesthetic injection, are asked to rate their level of pain on VAS, immediately following termination.

Second Visit:

Application of PA/LA prior to treatment of adjacent first molar of upper jaw, according to treatment allocation sequence number. Reactivity of the pulp to cold and electric stimulation, as well as the subjective sensation after manipulation by the aforementioned methods are reported.

### Outcomes

2.3

#### Primary outcome measures

2.3.1

Primary outcome measure to be assessed in this study is pain felt during the treatment, reported by the patient on a visual analogue scale (VAS) at the end of the treatment session.

#### Secondary outcome measures

2.3.2

Assessment of following secondary outcomes will be performed: changes in pulpal sensibility to electrical stimuli before and after LA/PA, evaluated by EPT (time frame: 25 minutes); changes in pulpal sensibility to cold stimulation before and after laser/PA by Cold-test—self-reported pain by the patient on VAS (Time Frame: 25 minutes); patient experience during LA/PA, evaluated by questionnaire; pain-related behavior during treatment, evaluated using the FLACC scale; heart-rate dynamics during the experiment, registered via pulse oximeter; need for additional local anesthesia infiltration.

#### Participant timeline

2.3.3

Each eligible patient undergoes 2 single-visit treatments of the 2 carious first upper jaw molars, receiving LA when undergoing treatment of 1 tooth and PA at the other visit during treatment of the homologous contralateral tooth. The 2 manipulations are performed by 1 operator, performing treatment of caries and restorative procedure. Outcomes are registered by the primary investigator in a clinical file (see supplementary data file S3 - “Clinical file”). A 7 to 21 day interval is allowed between one procedure and the other. The protocol to be used in the first procedure is randomly selected using a computer-generated list linked to sequence of enrollment in the trial.

#### Sample size calculation

2.3.4

Given the lack of comparable research and the unknown population standard deviation we conducted a pretest with 20 subjects and considered the behavior of this subgroup as population estimate. To estimate sample size for the primary outcome—pain felt during laser ablation of moderate carious lesion, according to the VAS scale—we applied a *t* test for paired groups (G∗ Power software version 3.1),^[13]^ since we have 2 groups (first upper molar in right and left quadrant) on the same patient.

The effect size was determined using the formula 

Where SD is the pooled standard deviation—an average of the standard deviations of the experimental and control groups. The error was set at 5% and the power test at 95%. According to the calculation, a sample of 37 patients will be necessary to detect differences in pain. Since drop-outs are unavoidable when collecting follow-up data, this number needs to be adjusted for the estimated drop-out rate. During the pre-test, we had a drop-out rate of 5% for collecting the follow-up data and if we anticipated a higher drop-out rate for this study, we conservatively allowed for a 10% drop-out rate. Adjusting the sample size for this drop-out rate results in a sample of 41 patients needing to be recruited.

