## Statistical methods

3

The unit of analysis will be the tooth for the split-mouth RCT (2 first permanent molars belonging to the same dental arch treated per patient). The data will be recorded and analyzed using SPSS 20.0. All data will be analyzed using an intention-to-treat analysis.^[14]^ Descriptive statistics will be calculated. Discrete variables will be summarized by frequencies or proportions. Continuous variables will be reported as means and standard errors or medians and range (depending on the distribution of the variables). Data will be checked for baseline differences between the treatment arms. If baseline differences do occur for any of the variables, they will be added to subsequent models to compensate for those differences using an analysis of covariance approach.

We will compare pain mean scores according to the visual analogue scale (VAS), containing numerical symbols. We will report the mean differences between groups and the associated 95% CIs. For the split-mouth RCT, with each patient being his or her own control, our statistical analysis will take into account the paired nature of data and the results will be analyzed by Student *t* test for paired samples.

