## Discussion

5

LA is a new alternative and a traumatic method that could help improving the quality of pediatric dental care. Different possible explanations have been suggested for low-level laser action (bio-photomodulation) regarding pain relief.^[15]^ Currently no consensus is reached regarding a detailed protocol with reliable laser parameter settings for pre-emptive LA, and some research lacks necessary parameter detail, presenting challenges to repeat or reproduce.^[11]^ Many studies nevertheless agree that to obtain pulpal analgesia, it is necessary to take advantage of low energy and power densities.^[3,8,11,16,17]^

The clinical adequacy of Er:YAG laser for achieving pre-emptive dental analgesia is investigated in a complex manner by pulp sensibility testing, along with assessment of subjective and objective pain during treatment of similar cases. This randomized controlled trial (RCT) trial is a well powered one-center split-mouth experimental study with two-way repeated measures design. The trial is double-blind, where patients and outcomes assessor are blinded for the study, involving only one operator, who cannot be blinded, and one primary investigator, reducing inter-individual variability from the estimates of the treatment effect. A disadvantage of this trial is the need to include positive patients with symmetrical and similar conditions, and many patients are not eligible. The following precautions are taken in account to minimize variables in results: eligible patients are selected from a narrow age group (10–12 years), classified as positive or definitely positive through Frankl behavior scale. Age of the patients is compliant with the need for full root development of teeth to be examined with EPT. Carious lesions are restricted to moderate caries diagnosed by ICDAS with code 03/04 on first upper molars without previous restorations. Focus of the trial is pain during treatment after pre-emptive laser or PA—the VAS scale is selected as means for subjective pain rating of the patient, while the FLACC scale is chosen to register pain-related behavior by the outcomes assessor.

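### The sample size for a paired t test is described with the average of the two arm SDs as standardiser, so 95% power at 37 pairs is supported only if the within-child correlation is 0.5 or higher, unless a conversion went unreported

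*Protocol article*

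**What the plan says.** All references are to the protocol article.

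- **Section 2.3.4, Sample size calculation.** The test used for sizing is named: "we applied a *t* test for paired groups (G∗ Power software version 3.1". The inputs come from a pretest of 20 children, and the authors "considered the behavior of this subgroup as population estimate". The standardiser is defined in words: "Where SD is the pooled standard deviation—an average of the standard deviations of the experimental and control groups". The error rate is 5% and the power 95%. The result is 37 patients, raised to 41 for drop-out.
- **Section 1.3, Trial design (text after Table 1).** A looser target appears: "a maximum permissible error *α* < 0.05 and *β* < 0.2".
- **Section 3, Statistical methods.** The primary comparison is a paired Student t test, and "our statistical analysis will take into account the paired nature of data".
- **Section 5, Discussion.** The design is described thus: "This randomized controlled trial (RCT) trial is a well powered one-center split-mouth experimental study".

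The text at hand gives no numerical effect size, mean difference, SD, SD of differences or within-child correlation.

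**The concern.** Each child contributes two VAS scores, one after laser and one after placebo. The paired t test works on the difference between them, and its error term is the SD of those differences. An average of the two arm SDs belongs to an effect size for independent groups. The two standardisers coincide only at one value of the correlation between a child's two scores, and the article gives no value for it.

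The 37 pairs, the 41 to be recruited and the Discussion's statement about power all rest on this input. If the correlation is lower than the calculation implicitly needs, the trial has less power for its primary outcome than readers are told, and a non-significant result would be less informative than it seems. The two scores come from different teeth treated 7 to 21 days apart (section 2.3.3), so a high correlation cannot simply be presumed.

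**Working it through.** **Inputs.** Paired t test, 37 pairs, 5% error, 95% power, SD defined as the average of the arm SDs (all section 2.3.4). Two assumptions are added: the 5% is two-sided, since sidedness is not stated, and the two arms have equal SDs unless noted.

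**Step 1: what the test needs.** For n pairs, power follows the noncentral t distribution with n − 1 degrees of freedom and noncentrality dz × sqrt(n), where dz = mean difference / SD of differences. With arm SDs s1 and s2,

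SD of differences = sqrt(s1² + s2² − 2·rho·s1·s2),

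which is SD × sqrt(2(1 − rho)) when s1 = s2 = SD. If d is the mean difference divided by the arm SD, then dz = d / sqrt(2(1 − rho)).

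**Step 2: the plan's own figure.** The 37 cannot be reproduced forward, because no effect size is given in the text at hand. Solving backwards, an effect of 0.609 gives exactly 95% power at 37 pairs, and 0.618 would already give it at 36. The entered value therefore lay between about 0.609 and 0.618 (one-sided: 0.551 to 0.559). The lower end, 0.609, is used below.

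**Step 3: read that value as d, as section 2.3.4 describes it.** Example for rho = 0.3: dz = 0.609 / sqrt(1.4) = 0.515.

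| rho | dz | power at 37 pairs | pairs for 95% power |
|---|---|---|---|
| 0 | 0.431 | 72% | 72 |
| 0.2 | 0.482 | 81% | 58 |
| 0.3 | 0.515 | 86% | 51 |
| 0.4 | 0.556 | 91% | 44 |
| 0.5 | 0.609 | 95% | 37 |
| 0.6 | 0.681 | 98% | 31 |
| 0.7 | 0.786 | above 99% | 24 |

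Power passes 80% at rho of about 0.17 and 90% at about 0.38.

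**Step 4: sensitivity.**

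- One-sided 5% gives a similar pattern: 75% at rho 0, 87% at 0.3, 95% at 0.5 and 98% at 0.6.
- At the upper end of the implied range the break-even shifts only slightly: 2(1 − rho) = (0.618/0.609)² = 1.03, so rho = 0.485.
- With unequal arm SDs the break-even rises. It is rho = (s1² + s2² − average²) / (2·s1·s2). For an SD ratio of 1.5 this is (1 + 2.25 − 1.5625)/3 = 0.56. For ratios of 1.25 and 2 it is 0.52 and 0.69.

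**The case against.** The best defence is that the error is inferred and not shown. The equation announced by "The effect size was determined using the formula" did not survive in the text available, and its absence is no fault of the plan. The software named can derive dz from the two group SDs and a correlation, so the authors may have converted correctly without saying so. This stands, and it makes every power figure above conditional. It does not remove the point: the sentence that survives defines the SD explicitly, and neither a correlation nor a conversion is mentioned.

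The shortfall may also be modest. The scores come from the same child, on homologous molars with similar lesions, treated by one operator, so a positive correlation is plausible. At rho of about 0.17 or more, 37 pairs still meet the beta bound under Trial design. That too stands, although the documents give no value of rho.

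A reader might infer more than the documents support:

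- **That 95% holds only at a correlation of exactly 0.5.** That is where the two standardisers coincide with equal SDs. Above it, power exceeds 95%.
- **That the trial is shown to be underpowered.** Rho is unknown, so even the direction of the discrepancy is open.
- **That pilot uncertainty can be quantified by placing a confidence interval around 0.609 as a dz seen in 20 children.** This contradicts the premise that 0.609 is not a dz. Caution about using a small pretest as the population is a separate, general matter.
- **That a high correlation would expose extra children to placebo alone.** Every child receives both procedures.

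**Conclusion.** The point holds as a mismatch between the stated standardiser and the stated test. As written, the 95% power at 37 pairs and the Discussion's statement about power are unsupported. Unless an unreported conversion was made, at least 95% power requires a within-child correlation of 0.5 or more with equal arm SDs, and a higher one if the SDs differ. Below that, power falls to 91% at rho 0.4 and to 72% at rho 0. These figures rest on a two-sided 5% test and an effect of 0.609 back-solved from the 37.

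The mismatch is certain on the text; the shortfall is conditional. The planned paired t test is appropriate, so the type I error, the estimated difference and its 95% CI are unaffected. What needs correcting is the stated power.

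**What to change.** 1. From the pretest, compute the SD of the within-child VAS differences (laser minus placebo) and recompute dz with it. This assumes the pretest children were scored under both procedures, which the paired calculation implies but the article does not say. If they were not, show power over a range of rho.
2. Keep recruitment at 41 and state the power that 37 evaluable pairs deliver. If a conversion was made, report the correlation used and the resulting dz.
3. State the sidedness of the 5%, and reconcile the 95% power in section 2.3.4 with the beta below 0.2 in section 1.3. The first satisfies the second, but a reader cannot tell which is the design target.
4. Qualify the Discussion's claim about power if the recomputed figure does not support it.

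The cost is a short recalculation on pretest data and edits to three places in the text, with no extra patients. The downside is that the stated power may become less favourable.
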